### Data management and monitoring

Upon conclusion of the treatment period, data will be completed and recorded on the original CRFs. No record will be missed or omitted, and the primary input of the data will not be permitted to be changed. Any corrections should be explained in the appended notes signed and dated by the researcher. Also, all data will be entered in an electronic database, following a standard data management protocol for data entry.

To protect confidentiality, written data will be stored in locked filling cabinets at the study sites with access limited to the researchers. Electronic data will be stored in a password-protected computer. After the trial, all documents will be preserved in the secure research archives at Dongguk University Oriental Hospital, and will only be available to the research team. All participants will have access to their personal data and the final study results.

Regular monitoring that will be clarified in a standard operating procedure will be conducted by an independent data monitoring committee. Monitors will evaluate whether the CRFs are properly written and whether the recruitment and intervention procedures are adequately performed according to the protocol.

### Statistical analysis

An independent statistician blinded to group allocation will perform statistical analysis on the full analysis set (FAS) and will also perform a pre-protocol (PP) analysis. Missing data will be replaced according to the principle of the last observation carried forward (LOCF) method.

Demographic and other baseline values will be analyzed using descriptive statistics for each group. For comparison of characteristics among the three groups, continuous data will be expressed as mean and SD and analyzed using analysis of variance (ANOVA) or the Kruskal-Wallis test. Categorical data will be presented as frequency and percentage and analyzed using chi-squared test or Fisher’s exact test.

The primary endpoint is the mean change in pain on the NRS from week 1 to week 6. To test the significance of changes in pain on the NRS between groups, we formulated two sets of hypotheses.

The first null hypothesis (H_01_) is that the EM and TIM groups have no difference in the true mean change of pain on the NRS before and after treatment. The first alternative hypothesis (H_11_) is that the EM and TIM groups have a difference in the true mean change in pain identified on the NRS before and after treatment.

The second null hypothesis (H_02_) is that the EM and usual care groups have no difference in the true mean change in pain on the NRS before and after treatment. The second alternative hypothesis (H_12_) is that the EM and usual care groups have a difference in the true mean change in pain on the NRS before and after treatment.

ANOVA or the Kruskal-Wallis test will be used to determine the significance of differences in the measured values before and after treatment in each group. To compare the three groups, analysis of covariance (ANCOVA) will be performed for the primary endpoint, with a fixed effect for the treatment group. Baseline pain on the NRS, age, Kellgren-Lawrence grade, and duration of KOA symptoms will be considered as covariates in this analysis. A *p* value below 0.05 will be considered significant for all analyses, and 95% confidence intervals (CIs) will be calculated.

The secondary outcome measures will be mean changes in values on four additional metrics: the 100-mm VAS, the K-WOMAC scale, the PGA, and the EQ-5D-5 L. These data will be analyzed using the same methods as for the primary outcome measure. Subgroup analyses will be conducted to determine the effect of sex, age, severity of pain, previous treatment, expected level of treatment, body mass index (BMI), and patterns of cold-heat and deficiency-excess [27] on the efficacy of EM and TIM.

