### Design and setting

This is a multicenter, randomized, open, assessor-blinded, parallel-group clinical trial. Eligible participants who meet the clinical criteria for KOA of the American College of Rheumatology (ACR) [18] will be enrolled. Two clinical research centers in Korea will participate: Dongguk University Bundang Oriental Hospital and Dongguk University Ilsan Oriental Hospital. A total of 138 participants with KOA will be randomly assigned to one of three groups (EM, TIM, or usual care) with a 1:1:1 ratio.

The study period is 12 weeks, and consists of a 6-week treatment phase and a 6-week follow-up phase. After randomization, participants in the EM and TIM groups will receive 12 sessions of treatment over 6 weeks. Participants in the usual care group will be assessed at 1, 4, and 6 weeks after baseline. Follow-up assessment by telephone will be conducted at 6 weeks after the end of treatment for all groups. Figure 1 outlines the trial procedures and Fig. 2 shows the schedules for enrollment, intervention, and assessments. The SPIRIT checklist is provided in Additional file 1.

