### Sample size

Sample size was estimated as described previously [19], which considered a change in the population mean on the numerical rating scale (NRS) for each group (1, EM group; 2, TIM group; 3, usual care group). The null and alternative hypotheses are:$$ {H}_{01}:{\mu}_1-{\mu}_2=0,\kern0.5em {H}_{02}:{\mu}_1-{\mu}_3=0 $$$$ {H}_{11}:{\mu}_1-{\mu}_2\ne 0,\kern0.5em {H}_{12}:{\mu}_1-{\mu}_3\ne 0 $$

H01 : the first null hypothesis

H02 : the second null hypothesis

H11 : the first alternative hypothesis

H12 : the second alternative hypothesis

μ1, μ2, μ3 : the true mean change of pain on the NRS before and after treatment (1: EM, 2: TIM, 3 : usual care)

We assumed that the true mean differences in pain on the NRS before and after treatment with EM and TIM were 12.25 (standard deviation (SD) 18.52) and 1.4 (SD 16.27), respectively. Thus, we calculated the sample size needed to achieve 80% power at a significance level of 0.05 using the following equation:$$ n=\frac{\left({\sigma}_1^2+{\sigma}_2^2\right){\left({Z}_5+{Z}_{\upbeta}\right)}^2}{{\left({\mu}_1-{\mu}_2\right)}^2}\approx 41 $$

σ1, σ2 : the true standard deviation (1 : EM, 2 : TIM)

α : significance level

β : power

Z : points on normal distribution to give required power and significance

The mean difference between the usual care group and the EM and TIM groups is expected to be larger than that between the EM and TIM groups. Thus, sample size was estimated larger because of using the mean difference between the EM and TIM groups.

Thus, the estimated sample size was 41 participants per group. Considering an anticipated dropout rate of 10%, we plan to include a total of 138 participants, with 69 participants per institution.

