### Outcome assessments

#### Primary outcome

The primary outcome measure will be the mean change in pain on the NRS from week 1 (before treatment) to week 6. Participants in the EM and TIM groups will be asked to indicate a number between 0 and 100 that best describes the intensity of pain every week and at week 12 (follow-up check): 0 usually represents “no pain at all”, whereas 100 represents “the worst pain imaginable” [21]. Participants in the usual care group will be assessed using the same method at weeks 1, 4, 6, and 12.

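### LOCF, the stated missing-data rule for the primary NRS change, biases the between-arm contrasts and gives intervals narrower than the observed data support

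*Protocol article*

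**What the plan says.** The Statistical analysis section of the protocol article fixes the rule: "Missing data will be replaced according to the principle of the last observation carried forward (LOCF) method". It states no other handling of missing values. The section also says that the statistician "will perform statistical analysis on the full analysis set (FAS) and will also perform a pre-protocol (PP) analysis"; the second of these is another analysis population, not another way of treating missing data.

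The outcome to which the rule applies is given in the same section: "The primary endpoint is the mean change in pain on the NRS from week 1 to week 6". For the comparison, "analysis of covariance (ANCOVA) will be performed for the primary endpoint, with a fixed effect for the treatment group", with baseline NRS among the covariates. The secondary outcomes are to be analysed in the same way.

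The NRS visits differ by arm. Under Primary outcome, EM and TIM participants give the number that "best describes the intensity of pain every week and at week 12 (follow-up check"), whereas "Participants in the usual care group will be assessed using the same method at weeks 1, 4, 6, and 12". The Design and setting section likewise has usual care assessed at weeks 1, 4 and 6.

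The Sample size section assumes that the mean changes under "treatment with EM and TIM were 12.25 (standard deviation (SD) 18.52) and 1.4 (SD 16.27), respectively". It gives no figure for usual care, but expects the difference from usual care to exceed the difference between EM and TIM.

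**The concern.** LOCF sets a dropout's week-6 pain to the last recorded rating. If pain is still changing, as the plan assumes for EM, the carried value holds only part of the change. The arm that improves more loses more, so the contrast between arms is distorted. The filled-in values also enter the ANCOVA as if they had been observed, so the analysis claims the precision of a trial with no dropout.

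Both primary hypotheses, EM against TIM and EM against usual care, rest on this analysis. For the second, a further feature matters: a missing week-6 value can be filled from any of weeks 1 to 5 in EM, but only from week 1 or week 4 in usual care. The carried values therefore differ in age by arm.

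**Working it through.** **Inputs from the protocol.** Assumed mean change: EM 12.25 (SD 18.52), TIM 1.4 (SD 16.27). Two-sided alpha 0.05, power 80%, dropout 10%, total 138 in a 1:1:1 ratio. NRS visits up to week 6: EM and TIM weekly; usual care weeks 1, 4 and 6. Week 1 is taken as the pre-treatment rating, as the Primary outcome section says.

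**Assumptions, not in the protocol.** Change is linear from week 1 to week 6. The last attended week L is uniform over 1 to 5. Dropout is completely at random with fraction f, equal in the arms unless stated. Usual-care change c is unknown and is varied. Positive change means improvement. Bias is the LOCF expectation minus the true week-6 difference, so a negative value understates EM's benefit.

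**The plan's sample size reproduces.** n = (18.52² + 16.27²) × (1.960 + 0.842)² / (12.25 - 1.4)² = 607.7 × 7.849 / 117.7 = 40.5, so 41 per arm. 41 / 0.9 = 45.6, so 46 per arm and 138 in total.

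**Share of the change that LOCF keeps.**
- EM and TIM: mean of (L - 1)/5 = (0 + 0.2 + 0.4 + 0.6 + 0.8)/5 = 0.40, so 0.60 is lost.
- Usual care: 0 for L = 1, 2, 3 and 0.6 for L = 4, 5; mean 1.2/5 = 0.24, so 0.76 is lost.

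**EM minus TIM (same schedule).** Bias = -f × 0.60 × 10.85. At 10%: -0.65. At 20%: -1.30.

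**EM minus usual care.** Bias = -f × 0.60 × 12.25 + f × 0.76 × c. With equal schedules it would be -f × 0.60 × (12.25 - c), so the part due to the schedule is f × 0.16 × c.

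| Usual-care change c | Bias, 10% dropout | Bias, 20% dropout | Schedule part, 10% |
|---|---|---|---|
| 0 | -0.73 | -1.47 | 0.00 |
| 1.4 | -0.63 | -1.26 | +0.02 |
| 6 | -0.28 | -0.56 | +0.10 |
| 12.25 | +0.20 | +0.39 | +0.20 |

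The sign turns at c = 7.35/0.76 = 9.7. The plan's expectation that the usual-care difference exceeds 10.85 means 12.25 - c > 10.85, that is c < 1.4. The relevant rows are therefore the first two, and LOCF works against EM.

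**Unequal dropout.** With c = 1.4, 15% dropout in EM and 5% in usual care give -0.15 × 7.35 + 0.05 × 0.76 × 1.4 = -1.05. The reverse split gives -0.05 × 7.35 + 0.15 × 0.76 × 1.4 = -0.21.

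**Interval width, by simulation.** Settings: 46 per arm, SD of change 17.4 (the root mean square of 18.52 and 16.27), equal correlation of 0.5 between weeks, EM 12.25, usual care set to 1.4, ANCOVA on baseline NRS.

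| | 10% dropout | 20% dropout |
|---|---|---|
| Mean 95% interval width, LOCF | 12.5 | 12.3 |
| Width with no missing data | 12.6 | 12.5 |
| Width with observed week-6 data only | 13.3 | 14.1 |
| Coverage of the true difference, LOCF | 94.6% | 93.1% |

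The ratios are 12.5/13.3 = 0.94 and 12.3/14.1 = 0.87. Over the settings tried, the shortfall was about 5-7% at 10% dropout; at 20% it was about 12%. The LOCF standard error at 10% (3.14) equals the spread of the LOCF estimates over repetitions (3.14). The interval is thus too narrow in that it claims full-data precision for the week-6 difference, and the lost coverage goes with the shift in the estimate. At 10% dropout, analysis of observed week-6 values and a likelihood-type estimate on the common visits both had bias near 0.

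**The case against.** The strongest reply is that little is at stake at the planned dropout. The bias stays below about 0.75 points against a planned 10.85, and coverage is close to nominal. That stands, and it limits the weight of the point. It does not make LOCF a sound primary rule, because the bias grows in proportion to dropout.

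A reader might infer that the unequal NRS schedule is what causes the bias and the narrow intervals. The documents do not support this. The narrow interval comes from single imputation and most of the bias from carrying unfinished change forward; both would remain with identical visits. The schedule plays no part in EM against TIM, and no arm difference is stated for the secondary-outcome visits.

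A reader might also infer that LOCF creates a spurious advantage for EM. That needs usual care to improve by more than about 9.7 points. A gap of 0.20 at 10% dropout arises only if usual care improves as much as EM, contrary to the Sample size section.

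Finally, a separate analysis plan may add sensitivity analyses. Their absence here is therefore no fault; the criticism is of the method that the protocol does fix.

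**Conclusion.** The point holds as a criticism of LOCF as the stated primary rule. EM minus TIM is understated by about 0.65 points at 10% dropout and 1.3 at 20%. For EM minus usual care, the plan's own expectation (usual-care change below 1.4) puts the understatement at 0.63 points or more at 10% dropout and about double at 20%. Intervals are about 5-7% and 12% narrower than the observed data support.

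The unequal schedule is a minor aggravator, for the NRS against usual care only: about 0.02 points at 10% dropout and a usual-care change of 1.4, and at most 0.20 over the range shown. Unequal dropout matters more. It is plausible because the Dropouts section removes those who receive too few moxibustion sessions, a rule that can apply only in EM and TIM; more dropout in EM than in usual care would enlarge the bias.

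These sizes rest on linear change, uniform timing of dropout and dropout at random. The protocol gives neither the timing nor the usual-care change. If neither arm changed over time, LOCF would leave the means unbiased under random dropout.

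**What to change.** For the primary analysis, replace LOCF with one of the following:
- multiple imputation that uses all recorded NRS ratings, followed by the planned ANCOVA; or
- an MMRM with treatment, visit, treatment-by-visit interaction, baseline NRS and the other named covariates, taking the week-6 contrasts.

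State the missing-at-random assumption on which either rests, and keep LOCF as a sensitivity analysis only. Imputation from all ratings has the advantage of using the weekly EM and TIM values, including week 5, the rating nearest the endpoint.

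The cost is a wording change in the protocol and analysis plan, best made before any analysis by arm since enrolment has begun, and slightly wider intervals. No new visits or data are needed.

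### Before-after changes within each group are assigned to ANOVA or Kruskal-Wallis, which are independent-samples tests; with positively correlated scores the within-group p values come out too large

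*Protocol article*

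**What the plan says.** All places are in the protocol article.

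- Statistical analysis, on change within groups: "ANOVA or the Kruskal-Wallis test will be used to determine the significance of differences in the measured values before and after treatment"; the sentence closes by locating these differences within each group.
- The sentence that follows it, on the comparison between groups: "To compare the three groups, analysis of covariance (ANCOVA) will be performed for the primary endpoint, with a fixed effect for the treatment group".
- Earlier in the same section, continuous baseline characteristics of the three groups are to be "analyzed using analysis of variance (ANOVA) or the Kruskal-Wallis test".
- Primary outcome: "The primary outcome measure will be the mean change in pain on the NRS from week 1 (before treatment) to week 6".
- Statistical analysis, on the threshold: a p "value below 0.05 will be considered significant for all analyses".
- Statistical analysis, on the secondary outcomes: "These data will be analyzed using the same methods as for the primary outcome measure".

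The article names no paired or repeated-measures test: no paired t test, Wilcoxon signed-rank test, repeated-measures ANOVA or Friedman test.

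**The concern.** The tests named for the before-after question are the ones used, correctly, to compare baseline characteristics of three independent groups. Before-after scores in one arm are two measurements on each participant. A test for independent samples ignores the correlation between them and therefore uses the wrong standard error.

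At stake are the within-group p values for pain on the NRS and for the secondary scales measured before and after treatment: VAS, K-WOMAC and EQ-5D-5L. The PGA is different, because the participant already rates improvement from baseline and there is no before-after pair to test. With positive correlation, which is what one would expect of two pain scores from one person, the error makes the p values too large, so a real change within an arm may be reported as not significant.

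**Working it through.** **1. The plan's own figure.** Inputs from the Sample size section: changes of 12.25 (SD 18.52) for electrical moxibustion (EM) and 1.4 (SD 16.27) for traditional indirect moxibustion (TIM). On the level and power it says "we calculated the sample size needed to achieve 80% power at a significance level of 0.05". The alternatives are two-sided.

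n = (18.52² + 16.27²)(1.960 + 0.842)² / (12.25 − 1.4)² = 40.5, rounded up to 41 per group. With 10% dropout, 41/0.9 = 45.6, so 46 per group and 3 × 46 = 138. Both stated figures reproduce. They rest on a difference between groups, so the choice of within-group test does not enter them.

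**2. Standard error.** Let each score have SD σ, and let the pre-post correlation be ρ. The document does not give ρ, so 0.3, 0.5 and 0.7 are assumptions.

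- True variance of the mean change: 2σ²(1 − ρ)/n.
- Variance used by an independent-samples test: 2σ²/n.
- Ratio of standard errors: k = 1/√(1 − ρ).

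**3. Actual type I error** of a nominal two-sided 5% test: 2[1 − Φ(1.96k)].

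**4. Power for the planned EM change.** With n = 41 and SD of change 18.52, the true standard error is 18.52/√41 = 2.892, and 12.25/2.892 = 4.235.

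- Paired t test (40 df, critical value 2.021): non-central t power is 0.985.
- Independent-samples test (80 df, critical value 1.990): it rejects only when the mean change exceeds 1.990 × k × 2.892, so power is about Φ(4.235 − 1.990k).

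| Assumed ρ | k | Type I error (formula) | Φ(4.235 − 1.990k) | Power |
|---|---|---|---|---|
| 0.3 | 1.20 | 0.019 | Φ(1.857) | 0.97 |
| 0.5 | 1.41 | 0.0056 | Φ(1.421) | 0.92 |
| 0.7 | 1.83 | 0.0003 | Φ(0.602) | 0.73 |

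Simulation of 40,000 trials per setting with n = 41 agrees: type I error 0.020, 0.007 and 0.0006, and power 0.97, 0.92 and 0.72. In a smaller simulation, Kruskal-Wallis behaved like ANOVA (for example, power 0.90 at ρ = 0.5 and 0.70 at ρ = 0.7), while the paired t and signed-rank tests kept a type I error close to 0.05.

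**5. Smaller changes lose more.** For an illustrative true change of 8 points, simulated power was about 0.77 with the paired t test. With ANOVA it was about 0.65, 0.48 and 0.22 at ρ = 0.3, 0.5 and 0.7.

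**6. Sign of the correlation.** At ρ = 0 the independent-samples test has the right size. At a negative ρ the p values would be too small (actual size 0.074 at ρ = −0.2).

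**The case against.** The strongest defence is that nothing primary hangs on this sentence. H01 and H02 compare groups, the next sentence gives that comparison to ANCOVA, and the sample size is built on the same comparison. This stands, and it is why the point is minor. The error is also conservative under positive correlation, so it does not create false positive findings. That stands too.

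Two milder readings of the sentence do not remove the fault:

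- ANOVA might be short for repeated-measures ANOVA. The text does not say so, and the alternative it names, Kruskal-Wallis, is the rank counterpart of one-way ANOVA and has no paired form.
- The sentence might mean a comparison of change scores between groups. From that, a reader might infer that the plan holds two competing primary tests, one unadjusted and one ANCOVA, with no rule between them. The documents do not support this: the sentence places the test within each group, and the three-group comparison is assigned to ANCOVA straight afterwards.

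A reader might also infer that efficacy will be claimed because one arm changed significantly and another did not. The protocol nowhere says so. That misuse could follow any within-group test, a paired one included, so it is not a result of choosing ANOVA.

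**Conclusion.** Wrong as written, minor in severity. An independent-samples test is stated for paired data, and the rule that secondary outcomes follow the primary methods extends it to VAS, K-WOMAC and EQ-5D-5L. This is a method named wrongly, not a detail left to an analysis plan.

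For ρ between 0.3 and 0.7, the actual type I error runs from about 2% down to under 0.1%, and power for the planned EM change from about 97% down to about 72%, against about 98% with a paired test. These figures rest on the assumed ρ, on equal SDs before and after treatment, on roughly normal scores and on 41 analysed participants.

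Two stronger conclusions are not supported. A reader who applies the usual non-central t for two independent groups would get power of about 84% at ρ = 0.5 and 63% at ρ = 0.7. Those losses are too large, because that formula assumes the very independence that is absent; the mean change keeps its smaller paired variance. Nor does the error undermine the tests of H01 and H02 or the total of 138.

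**What to change.** Replace the sentence on before-after differences with wording such as: Change from week 1 to week 6 within each group will be reported as the mean change with its 95% confidence interval; where a p value is given, it will come from a paired t test or a Wilcoxon signed-rank test. H01 and H02 will be decided by the corresponding ANCOVA contrasts.

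The second sentence makes explicit what the section already implies and closes off the reading that there are two primary tests. The passage on secondary outcomes can still refer to the same methods, provided it notes that PGA is itself a rating of change and has no before-after test.

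The cost is a small edit to the analysis section, made before the data are analysed. Data collection, sample size and the primary analysis do not change.

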### Randomization and blinding

Eligible participants will be randomly assigned to one of three groups (EM, TIM, or usual care) with a 1:1:1 ratio. Randomization will be performed by an independent statistician with no clinical involvement in this trial, by use of a computerized random number generator through the stratified block method of SAS (SAS Institute Inc., Cary, NC, USA). The random numbers will be concealed using sequentially numbered, opaque, sealed envelopes. After the enrolled participants have completed all baseline assessments, the envelopes will be provided to doctors of traditional Korean medicine who will perform the moxibustion treatments. Allocation concealment will not be revealed until the final data analysis report is completed. This is an open clinical trial. Thus, the researcher who is blinded to the allocations will not participate in the treatment, but will perform the outcome assessment to reduce selection bias.

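### The primary ANCOVA leaves out centre, the most likely stratum of a stratified randomisation, which can make intervals somewhat too wide and tests conservative

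*Protocol article*

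**What the plan says.** All references are to the protocol article.

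- **Randomization and blinding:** allocation to the three groups is 1:1:1 and is generated "by use of a computerized random number generator through the stratified block method of SAS". The section does not say what the strata are.
- **Design and setting:** "Two clinical research centers in Korea will participate".
- **Sample size:** "we plan to include a total of 138 participants, with 69 participants per institution".
- **Statistical analysis:** "analysis of covariance (ANCOVA) will be performed for the primary endpoint, with a fixed effect for the treatment group". The covariates follow: "Baseline pain on the NRS, age, Kellgren-Lawrence grade, and duration of KOA symptoms will be considered as covariates in this analysis". Centre appears nowhere in this section. Its closing paragraph applies the same methods to the secondary outcomes.

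**The concern.** When randomisation is stratified by a factor that predicts the outcome, the arms are balanced on that factor, so it no longer adds to the true variance of the treatment difference. A model without the factor does not know this. It leaves the between-stratum variation in the residual and reports a standard error that is larger than the true one. The estimate is not biased, but part of the precision bought by stratifying is lost.

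With two centres and an equal planned number at each, centre is the obvious candidate for the stratum. The article writes the primary model out with four named covariates, and centre is not one of them. At stake is some precision on both primary comparisons, in a trial sized with almost no margin above 80% power.

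**Working it through.** **Inputs from the Sample size section.** The assumed mean changes for EM and TIM "were 12.25 (standard deviation (SD) 18.52) and 1.4 (SD 16.27), respectively"; power 80%; significance level 0.05, two-sided by the stated alternatives; 41 per group; 10% dropout; 138 in total.

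**Reproducing the plan's figures.**

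- Difference: 12.25 − 1.4 = 10.85.
- Pooled SD: √((18.52² + 16.27²)/2) = √(607.70/2) = 17.43.
- n per group: 607.70 × (1.960 + 0.842)² / 10.85² = 40.5, so 41.
- Dropout: 41/0.9 = 45.6, so 46 per group; 46 × 3 = 138; 138/2 = 69 per centre. If arms are balanced within centre, 69/3 = 23 per arm per centre.

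The plan's figures reproduce.

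**Effect of leaving centre out.** Let the mean NRS change differ between the two centres by D, after the listed covariates. With two equal centres balanced by arm, omitting centre adds D²/4 to the residual variance. The reported standard error is then multiplied by

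f = √(1 + D²/(4 × SD²)), with 4 × SD² = 4 × 303.85 = 1215.4.

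The true standard error at 41 per group is 17.43 × √(2/41) = 3.85. From this:

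- 95% half-width = 1.96 × 3.85 × f = 7.55 × f;
- two-sided type I error = 2 × (1 − Φ(1.96 × f));
- power = Φ(10.85/3.85 − 1.96 × f).

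The documents give no value for D, so the first column is an assumed range that includes zero.

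| D (NRS points, assumed) | f | 95% half-width, EM vs TIM | Wider by | Type I error | Power |
|---|---|---|---|---|---|
| 0 | 1.000 | 7.55 | 0% | 0.050 | 80.5% |
| 5 | 1.010 | 7.62 | 1.0% | 0.048 | 79.9% |
| 10 | 1.040 | 7.85 | 4.0% | 0.041 | 78.2% |
| 15 | 1.089 | 8.21 | 8.9% | 0.033 | 75.3% |

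With centre in the model the half-width stays at 7.55 and power at 80.5% in every row, by the same normal approximation.

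**Check by simulation.** Three-arm ANCOVAs with one baseline covariate were simulated, with 23 per arm per centre and about 11% random loss, 6,000 runs for each D. The ratio of interval width without centre to width with centre was 0.999, 1.010, 1.041 and 1.090 for D = 0, 5, 10 and 15, which agrees with f. Random loss did not disturb the balance enough to matter.

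**The case against.** **The stratum is not named.** A reader might infer that the analysis contradicts the randomisation. The article does not establish that. If the strata were Kellgren-Lawrence grade, age or baseline pain, the listed covariates would already cover them. The 23 per arm per centre also presupposes balance within centre. This stands: centre as stratum is an inference, though a strong one in a two-site trial with equal planned numbers and no other factor mentioned for stratification.

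**The loss may be zero.** A reader might also infer that the intervals are too wide as a matter of fact. They are so only if centre predicts NRS change. A 10-point centre difference would be nearly as large as the whole assumed EM–TIM effect of 10.85, and both hospitals belong to one university. This stands too, and it keeps the likely loss small.

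**Nothing shows that the centres differ.** It is tempting to argue that practitioners, assessors and the choice of extra tender points vary by site. No section says so. Quality assurance describes shared training and supervised treatment, and the Discussion speaks of one independent researcher making all assessments. The point should not rest on assumed differences in practice.

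**It may be left to the SAP.** The article is condensed, and its verb for the covariates leaves some room. Silence about the final model would be no finding. But the article does give a specific covariate list, and that list omits the likeliest design factor. The objection lowers the certainty and does not remove the point.

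**Conclusion.** The point holds in conditional form. The stated model omits centre although allocation is stratified and centre is the most likely stratum. If the strata are centres and centre is prognostic, inference is conservative: intervals for EM against TIM are about 1% to 9% wider for assumed centre differences of 5 to 15 NRS points, and power falls from 80.5% to between 79.9% and 75.3%. With no centre effect nothing is lost. The treatment estimate is unbiased, and type I error stays at or below 0.05 throughout.

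The figures assume that the plan's pooled SD of 17.43 is the within-centre residual SD, that the two centres are equal in size and balanced by arm, and that 41 per group are analysed. If the covariates reduce the residual SD, the same D widens the interval proportionally more. The factor f does not depend on the treatment effect, so with the same residual SD it applies equally to EM against usual care. This is a modest, cheap improvement and not a threat to validity.

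**What to change.** In the Statistical analysis section, add centre as a fixed effect in the primary ANCOVA, together with any other factor that was used to stratify the randomisation list and is not already a covariate. Do the same in the analyses of the continuous secondary outcomes, which follow the primary method. The randomisation specification will show which factors apply.

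The cost is one degree of freedom for centre. With 41 × 3 = 123 participants analysed, three group means and one parameter for each of four covariates, the residual degrees of freedom go from 123 − 7 = 116 to 115. The sample size does not change.
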